### Randomization and blinding

Patients will be informed of the procedure but they will be blinded to which is the intervention (high fat or low fat meal). Stratified blocked randomization will be performed accordingly to being asthmatic or obese. This methodology was chosen despite acute changes are the aim, to exclude and evaluate the intervention order in the studied outcomes. Equal number of participants will be allocated to each group.

Allocation concealment will be prevailed as investigator will only know the intervention order for that participant at the moment the meal is provided. Exercise challenge and outcome assessment, namely urine, blood sample collection, exhaled breath condensate and lung function will only be performed by another investigator blinded to the meal order.

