#### **4.1.5. Physical activity reduction effect on immune response (V)**

This is a randomized controlled trial where participants, after a run-in period and eligibility evaluation, will be randomized to an intervention consisting in a reduction of physical activity by 50% or maintaining habitual physical activity for two weeks. Participants will be recruited from the same population as the meal-exercise challenge study and stratification will be done accordingly to having asthma and  $BMI \geq 30 \text{ kg/m}^2$  in order for both characteristics could be balanced between groups.

Participants will be at baseline characterized for their nutritional status, dietary habits and physical activity through questionnaire and basal assessment of all sports activity practiced during a week. Also generic quality of life questionnaire will be applied. A pedometer and accelerometer will be used to monitor physical activity. After this run-in period, if they have an adequate physical activity they will be allocated randomly to one of the interventions. Calculation of physical activity reduction will be performed individually, and a daily steps target will be demanded for each group. Both groups will use a pedometer during 3 weeks, except during the night or at circumstances that the device might be damaged (bath). They will be able to monitor if they achieved or exceeded the target number of steps for that day. Keeping the same regular diet without any new changes will be requested and new recall dietary assessment will be also performed in the end of the study. Immune function mediators will be the primary outcome to be assessed before and after the intervention period in both groups. As secondary outcomes endocrine and metabolomic evaluation will be performed.

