#### Randomization

Stratified blocked randomization will be performed accordingly to being asthmatic or obese. This methodology was chosen in order for both groups to be balanced for intervention comparison. Neither the participants or investigator team will be blind to the intervention procedure as there is a need to monitor number of steps/day to be compliant with the prescribed physical activity diary (keeping the same mean steps or reducing by 50% the number of steps/day). Equal number of participants will be allocated to each group.

Allocation concealment will be prevailed as investigator and participant will only know the intervention that they will be submitted at the second visit.

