#### Intervention:

At baseline the included subjects will all collect blood samples, urine and exhaled air condensate. Then they will receive a list of indications adapted to their usual physical activity previously assessed in order for them to reduce by 50% their mean number of steps per day. As an example, they will be advised to: take the elevators instead of the stairs and riding car instead of walking or bicycling, reduce daily exercise training. The other participants will keep the same activity, also a number of target steps will be performed. Participants will not have knowledge of the mean number of steps that they usually performed, so both groups will receive specific written indications, but they will not know which will represent the intervention. No other contact will be done, but contact availability will be possible at anytime with investigators for any doubt. During the intervention the respiratory symptoms questionnaire will be given for them to fill in if they had an respiratory infection (**Attachment-1**)

After intervention all participants will deliver the pedometer. Blood, exhaled air condensate and urine will be collected. A questionnaire to evaluate nutritional assessment, quality of life (SF-36) and asthma control in patients with asthma will be performed.

The mediators that will be evaluated are: metabolomic markers, immune function and inflammatory measures (leukocytes, lymphocytes, neutrophils, lymphocytes subpopulations and cytokine reduction, IL-1, IL-6), endocrinological markers (insulin, resistin, adiponectin, PAI-1, leptin).

At the end of the study each patient will receive an individualized nutritional plan and physical activity indications performed by a nutritionist and a physician.

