#### **4.2.10. Immune-Endocrine and metabolomic mediators assessment (II, IV, V)**

Urine, blood and saliva samples will be collected to assess immune, endocrine and metabolomic assessment markers.

In urine samples metabolomic analysis will be performed with the same protocol described for exhaled breath condensate. But, samples will be collected and immediately frozen at -80°C, then only those samples that have been related to the outcome, respiratory infections in the swimmers cohort or those that completed all protocol of the clinical trials will be used.

Saliva will be collected as previously published[61], subjects will set quietly and with an initial swallow to empty the mouth, un-stimulated whole saliva will be collected by expectoration into a pre-weighted vial for 2 min with eyes open, head tilted slightly forward and making minimal oro-facial movement and saliva flow rate (ml/min) will be determined by weighing saliva density. Duplicate saliva samples can be analyzed for secretory IgA (S-IgA) using ELISA kit. The S-IgA secretion rate will be calculated by multiplying the S-IgA concentration by saliva flow rate

Blood will be obtained by venepuncture from an antecubital vein and will be collected into two Vacutainer tubes containing EDTA, 7ml and two serum-standard tubes 10 ml. Two of the samples with serum and plasma will be centrifuged and then stored -20°C. Hematological parameter, total and differential leukocyte counts will be performed in an automated cell-counter. Lymphocyte subpopulations (CD3, CD4, CD8, CD19, CD56) can be determined by flow cytometry with a three-color flow, in order to enumerate total T cell, T helper, T cytotoxic, B

and NK cells. Side-scatter and forward scatter will be use to gate lymphocyte population by morphology and at least 10 000 lymphocyte events will be acquired per analysis.

Serum Immunoglobulins IgA, IgG, IgM can be measured by nephelometry. Cytokines, IL-1, IL4, IL8 IL-10 also could be measured using commercial ELISA. Insulin, adiponectin, leptin, resistin, tumor necrosis factor- $\alpha$ , serpin/type-1 plasminogen activator inhibitor and interleukin-6 measured by multiplexed bead immunoassay, as previously described[62]. Plasma fatty acids concentration will possibly be analyzed using gas chromatography as previously described[63].

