measures vertical acceleration and deceleration in 1-min epochs. Participants will put it on the right mid-axillary line of the hip on an elastic belt or clip and wear during one week period and then remove it for sleep or any activity that could cause harm to either the monitor or another person. This can be used to monitor light moderate, hard and very hard activity [68]: light intensity will be considered as <3 metabolic equivalents (METs), moderate 3–5.99 METs, hard 6–8.99 METs, and very hard >8.99 METs. Activity counts cut-off, will correspond to MET levels by the equation  $(\text{cnts}/\text{min}) = (5.99 - 1.439008) / 0.000795$  [68]. Pedometer is also a validated method to evaluate physical activity it will be used in association with an accelerometer for baseline physical activity assessment. To register the number of daily steps the subjects will be instructed to wear the pedometer placed in the waistline above the knee, as previously published [29] and it will be worn for 1 week, being removed for sleep or other activity that could damage the device, namely bath.

Pedometer will be further used for intervention of reduced physical activity (V). In this study, accordingly to the previous baseline number of steps per day were instructed to reduce daily steps in more than 50%. For that accordingly to the assessed physical activity in baseline evaluation in those that performed >3500 steps/day, will be recommended to use elevators instead of stairs, riding in cars instead of walking or bicycling during 2 weeks period. A limit of steps/day will be calculated for each participant and they will be able to see if the limit was achieved. All steps will be recorded in the display and stored in the device for posterior computer download.

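### Study V unblinds the whole investigator team because steps must be monitored, a reason that does not extend to sample collection and handling, lymphocyte gating or analysis choices

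*Protocol*

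**What the plan says.** Study V randomises participants to two weeks of halved or habitual physical activity. The blinding statement, in the Randomization part of section 4.1.5, is that "Neither the participants or investigator team will be blind to the intervention procedure as there is a need to monitor number of steps/day". No other reason is given. On the outcome, section 4.1.5 states: "Immune function mediators will be the primary outcome to be assessed before and after the intervention period in both groups". Endocrine and metabolomic measurements are secondary.

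The Intervention part of the same section says that both groups receive written step instructions but that "they will not know which will represent the intervention".

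The laboratory methods for Studies II, IV and V are in section 4.2.10. On flow cytometry it says: "Side-scatter and forward scatter will be use to gate lymphocyte population by morphology". Section 4.3, which covers all five studies, makes log transformation and the choice between parametric and non-parametric tests depend on the observed distribution.

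For Study IV, section 4.1.4 (Randomization and blinding) says that the exercise challenge, the collection of blood, urine and breath condensate, and lung function "will only be performed by another investigator blinded to the meal order".

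**The concern.** In a trial of activity reduction the participant can hardly be blinded in full, and whoever sets the step target has to know it. The other roles can usually still be blinded: those who collect and process samples, those who make judgements on the readouts, and those who decide how the data are analysed. Study V gives up blinding for the whole team on the strength of a reason that concerns one task. If the arm is known when a sample is handled, a gate is drawn or a transformation is chosen, a difference between the arms can be created or hidden without anyone intending it. A laboratory primary outcome is one for which this is easy to avoid.

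**Working it through.** No arithmetic applies. The protocol gives no effect size, standard deviation or power for Study V (section 4.3.4 says that a power analysis was precluded), so there is no figure to reproduce and no input from which to size a bias. The check sets the passages side by side.

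1. **How far the stated reason reaches.** Section 4.1.5 says of the participants: "They will be able to monitor if they achieved or exceeded the target number of steps for that day". Section 4.2.11 says of the pedometer: "All steps will be recorded in the display and stored in the device for posterior computer download". On contact during the two weeks, section 4.1.5 says: "No other contact will be done, but contact availability will be possible at anytime with investigators for any doubt". So the participant and the device do the daily monitoring, and staff are needed to set the target, answer queries and download the data. None of this requires the person who draws or processes blood, gates cells or analyses data to know the arm.

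2. **Which steps are left unprotected.**
   - *Sample collection.* Baseline samples are taken before the step instructions are handed out, so their collection is protected by the order of events. Post-intervention samples are not. Section 4.1.5 has participants return the pedometer and give samples after the intervention, and no separation of roles is described.
   - *Gating.* Lymphocyte subpopulations are among the Study V immune markers in section 4.1.5, and section 4.2.10 gates them by morphology, which involves operator judgement.
   - *Analysis.* Section 4.3 leaves transformation and test to the observed distribution. Section 4.3.4 names paired t-tests for the changes in Study V, which narrows the choice but does not remove the transformation step.
   - No section provides coded samples, a blinded assessor or a masked data set for Study V. Section 9 lists physicians, nutritionists and sports scientists and names no separate laboratory or analysis role.

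3. **Which steps are less exposed.** Under section 4.2.10, total and differential leukocyte counts come from an automated counter, IL-1 from a commercial ELISA and IL-6 from a bead immunoassay. Subpopulations are described only as something that can be determined, so the gating step may not be carried out.

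4. **Feasibility.** Study IV draws on the same recruits and measures largely the same immune markers. There the protocol already assigns collection and outcome assessment to a blinded investigator.

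5. **Consistency.** The Randomization text says that participants are not blind; the Intervention text says that they will not know which instructions are the intervention. The two statements cannot both stand unqualified.

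**The case against.** The strongest reply is that unblinded laboratory work is inferred from silence. The text declares the investigator team unblinded; it does not say who will run the assays. Section 9 says that laboratory analysis awaits funding and that samples will be stored until then, so the work may go to people who never learn the arm. Tube coding and analyst masking are also often left to a laboratory manual or a statistical analysis plan, which is not at hand. This stands as a limit: the protocol cannot be read as saying that gating or analysis will be done with the arm known. It does not remove the point, because the protocol makes an explicit choice about the whole team, gives one reason for it, and that reason is too narrow.

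Further limits also stand. The blinding in Study IV covers the exercise challenge, collection and outcome assessment; it does not mention gating or the analyst, so it shows that blinded collection and assessment are feasible and no more.

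Three stronger readings are tempting. A reader might infer that the whole primary outcome is open to bias, but most of the named immune assays leave little to the operator. A reader might add compound identification in metabolomics, or decisions on assay repeats and outliers; the former concerns a secondary outcome and the latter appear nowhere in the protocol. A reader might also quote an inflated false-positive rate, but that needs an assumed shift in one arm for which the document offers no basis.

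**Conclusion.** The point holds in a limited form. Section 4.1.5 unblinds the entire Study V team for a reason that covers only those who set and check step targets, and nothing else in the protocol protects post-intervention collection and processing, morphological gating or the distribution-dependent analysis choices. The exposure lies mainly in those steps. The size of any bias is unknown and cannot be computed from the document. The conclusion assumes that no laboratory manual or analysis plan outside the protocol already provides masking; if one does, the protocol text should still be corrected to agree with it. This is a worthwhile correction to make before samples are processed, not a fault that by itself invalidates the trial.

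**What to change.** In the Randomization part of section 4.1.5:

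- Limit the unblinded role to the staff who issue step targets and download pedometers. Have pedometers returned to them and not to whoever collects the post-intervention samples.
- Label blood, urine and condensate samples with a code that shows neither arm nor visit.
- Keep gating masked to arm, and hold the analysis data set with coded groups until it is locked, so that transformation and test are chosen without knowledge of arm.
- Reconcile this text with the Intervention part on whether participants know their arm. Say plainly what they are told and what they are not.

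The cost is minor work on sample coding and on keeping the allocation list apart from the laboratory and analysis data. No extra staff, visits, samples or procedures are needed. The change has to be in place before the post-intervention samples are collected and processed, because masking cannot be restored afterwards.

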#### Intervention:

At baseline the included subjects will all collect blood samples, urine and exhaled air condensate. Then they will receive a list of indications adapted to their usual physical activity previously assessed in order for them to reduce by 50% their mean number of steps per day. As an example, they will be advised to: take the elevators instead of the stairs and riding car instead of walking or bicycling, reduce daily exercise training. The other participants will keep the same activity, also a number of target steps will be performed. Participants will not have knowledge of the mean number of steps that they usually performed, so both groups will receive specific written indications, but they will not know which will represent the intervention. No other contact will be done, but contact availability will be possible at anytime with investigators for any doubt. During the intervention the respiratory symptoms questionnaire will be given for them to fill in if they had an respiratory infection (**Attachment-1**)

After intervention all participants will deliver the pedometer. Blood, exhaled air condensate and urine will be collected. A questionnaire to evaluate nutritional assessment, quality of life (SF-36) and asthma control in patients with asthma will be performed.

The mediators that will be evaluated are: metabolomic markers, immune function and inflammatory measures (leukocytes, lymphocytes, neutrophils, lymphocytes subpopulations and cytokine reduction, IL-1, IL-6), endocrinological markers (insulin, resistin, adiponectin, PAI-1, leptin).

At the end of the study each patient will receive an individualized nutritional plan and physical activity indications performed by a nutritionist and a physician.

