#### **Procedures**

After recruitment an interview will be performed to verify if patient meets the inclusion criteria for study inclusion. This interview will assess weight and height, previous history of asthma and its control, presence of co-morbidities and availability to the study intervention and follow-up. If eligible, a run-in period will be performed that include: baseline assessment and a 7 week daily assessment of physical activity by a pedometer and accelerometer.

Baseline assessment will consist in: nutritional assessment, quality of life questionnaire (**Attachment 2**), asthma control questionnaire in asthmatic patients (**Attachment 7**), blood pressure, rest heart rate measurements, pupillometry, lung function measured by spirometry and bronchodilation, atopy assessed by skin prick tests, basal physical activity evaluated by Baecke (**Attachment 8**) and International Physical Activity questionnaire(**Attachment 9**). Physical activity will be also accessed by accelerometer and pedometer; only subjects that perform more than 3500 steps/day will be included. All other participants that are not eligible will receive dietary and physical activity written recommendations.

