#### 4.3.1. Cross-cultural translation and Validation of WURSS (I)

For statistical analysis of questionnaire validation factorial analysis will be used for content validity evaluation using the 7 identified domains of WURSS-21 plus headache, body-ache and fever, which are included in WURSS-24. This approach combines exploratory and confirmatory procedures, using weighted least square estimates employing diagonal weight matrix techniques to seek common factors between the domains; all questioned items will be included in the analysis. Convergent validity will be provided by Pearson correlations between WURSS-21 scores in the first day and SF-36 scores in the third, as this measures health state in the last 4 weeks. For criterion validity sensitivity, specificity and predictive positive values will be calculated, as well as area under the curve. For internal consistency Cronbach's alpha coefficient in each domain based on the average of scores from the first three days will be calculated and also comparison between the first and last day. To evaluate each day, responsiveness index will be calculated which is equal to minimal important differences (MID)/ $\sqrt{(2\text{mean squared error})}$ .

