### Questionários de Controlo da Asma e da Rinite (Asthma Control Questionnaire e CARAT)

|                                                                                                                                                                                                               |                                    |                                     |                                        |                                     |
|---------------------------------------------------------------------------------------------------------------------------------------------------------------------------------------------------------------|------------------------------------|-------------------------------------|----------------------------------------|-------------------------------------|
| P1 – Durante as últimas 4 semanas , quanto tempo é que a asma o/a impediu de fazer as suas tarefas habituais no trabalho, na escola/universidade ou em casa?                                    |                                    |                                     |                                        |                                     |
| 1 – Sempre                                                                                                                                                                                             | 2 – A maior parte do tempo  | 3 – Algum tempo              | 4 – Pouco tempo                 | 5 – Nunca                    |
| P2 – Durante as últimas 4 semanas , quantas vezes teve falta de ar?                                                                                                                             |                                    |                                     |                                        |                                     |
| 1 – Mais de uma vez por dia                                                                                                                                                                            | 2 – Uma vez por dia         | 3 – 3 a 6 vezes por semana   | 4 – Uma a duas vezes por semana | 5 – Nunca                    |

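### Study V repeats SF-36 and asthma control after two weeks of intervention using four-week recall, so half of the final recall window precedes randomisation

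*Protocol*

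**What the plan says.** Section 4.1.5 of the protocol describes Study V as a randomised comparison of "reduction of physical activity by 50% or maintaining habitual physical activity for two weeks". Section 4.2.11 repeats the length: "riding in cars instead of walking or bicycling during 2 weeks period".

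The baseline assessment (4.1.5, Procedures) includes the quality-of-life questionnaire of Attachment 2 (SF-36 v2) and, for participants with asthma, the asthma-control questionnaire of Attachment 7. After the intervention (4.1.5, Intervention): "A questionnaire to evaluate nutritional assessment, quality of life (SF-36) and asthma control in patients with asthma will be performed". No delay between the end of the intervention and this visit is stated.

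On recall, Section 4.3.1 explains the timing of the SF-36 in Study I by saying "as this measures health state in the last 4 weeks". Each of the five items printed in Attachment 7 refers to the "últimas 4 semanas". No shorter-recall version or changed instruction is given for Study V.

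Section 4.1.5 names immune function mediators as the primary outcome and endocrine and metabolomic evaluation as secondary. SF-36 and asthma control appear only among the visit procedures. Section 4.3.4 plans an analysis of change from baseline to after the intervention, in general terms.

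**The concern.** A before-and-after measure of a two-week intervention should describe the two weeks. A form that asks about four weeks, completed when the intervention ends, also asks about two weeks in which nobody had yet been allocated. Both arms share those two weeks, so the expected result is a smaller difference between arms, not a bias towards one of them.

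What is at stake is how a null result would be read. If step reduction affects quality of life or asthma control, the four-week forms will tend to understate it. Asthma is a stratification factor in Study V, and the asthma-control form is the only asthma-specific measure listed for the final visit, so a reader may well look to it. No later analysis can recover a two-week state from a four-week answer. The forms and the length of the intervention are both fixed in the protocol.

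**Working it through.** **Inputs**
- Intervention length: 14 days (4.1.5 and 4.2.11).
- Recall: 28 days for the SF-36 (the protocol's own statement in 4.3.1) and 28 days for all five printed asthma-control items (Attachment 7).
- Run-in: 7 days in 4.1.5, Participants, but 7 weeks in 4.1.5, Procedures. "Both groups will use a pedometer during 3 weeks" agrees with one week of run-in plus two of intervention. The two statements need to be reconciled, but the first result below does not depend on them.
- Planned size: 60 randomised (Summary), equal allocation (4.1.5, Randomization), so 30 per arm.

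The protocol gives no power or sample size for these questionnaires, so there is no stated figure to reproduce.

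**1. Share of the final window before randomisation**

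(recall − intervention) / recall = (28 − 14) / 28 = 50%.

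Run-in length does not enter. A delayed final form would lower the share: (14 − 3)/28 = 39% at 3 days, (14 − 7)/28 = 25% at 7 days, 0% at 14 days. No delay is planned.

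**2. Effect on the contrast**

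Let w be the weight that respondents give to the intervention days. A true between-arm difference d then appears as w × d. With all 28 days weighted equally, w = 14/28 = 0.5 and d appears as d/2. If recent days count for more, w is above 0.5 and the loss is smaller.

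Illustration (assumed case): a participant has no breathlessness before randomisation and four episodes a week during the intervention. The intervention period alone falls in category 3 of the second Attachment 7 item (3 to 6 times a week). Averaged over four weeks it is (0 + 0 + 4 + 4)/4 = 2 a week, which is category 4 (once or twice a week). One category of worsening disappears through the recall wording.

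**3. Effect on power: two bounding models, both with equal weighting**

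*Noise unrelated to the days recalled (SD fixed).* The effect halves and the SD does not, so the sample-size factor is 1/0.5² = 4. With 30 per arm and an assumed two-sided alpha of 0.05, 80% power needs (1.960 + 0.842) × √(2/30) = 0.72 SD. Halved to 0.36 SD, power is about 29%, and 80% would need about 4 × 30 = 120 per arm.

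*Independent daily variation σ², a stable person effect and no response error.* The analysis uses change from baseline, so days common to both windows cancel. With k shared days the variance of the change is 2(28 − k)σ²/28². For matched 14-day windows without overlap it is 2σ²/14 = σ²/7. The sample-size factor is the variance ratio divided by 0.5²:

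| Baseline form completed | Shared days k | Variance of change | Factor |
|---|---|---|---|
| At randomisation | 14 | 28σ²/784 = σ²/28 | (1/28)/(1/7) × 4 = 1.0 |
| 7 days earlier | 7 | 42σ²/784 = 3σ²/56 | (3/56)/(1/7) × 4 = 1.5 |
| 7 weeks earlier | 0 | 56σ²/784 = σ²/14 | (1/14)/(1/7) × 4 = 2.0 |

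The factor therefore runs from about 1 to about 4. The protocol gives nothing that would narrow the range.

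**The case against.** The best case for leaving the plan alone is that these are not declared outcomes. The protocol attaches no hypothesis, comparison or power to SF-36 or asthma control in Study V, so a blunted score damages no stated claim. That stands, and it limits the weight of the point. It does not remove it, because the forms are collected before and after, and Section 4.3.4 analyses exactly that kind of change.

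The instruments can also be checked only in part. The SF-36 text is not reproduced under Attachment 2, so its recall rests on the general statement in 4.3.1 and need not hold for every item. Attachment 7 is headed with two instruments but prints one set of five items. The final-visit text cites no attachment, so it is an inference that the baseline forms are reused. These are fair qualifications, but everything that is printed says four weeks.

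Several stronger readings are tempting and are not supported:

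- **That half of the final score describes earlier time.** Only half of the recall window is shown to do so. How respondents weight days is unknown.
- **That effects are diluted in both arms.** The control arm keeps its habitual activity and has no step-reduction effect to dilute. What shrinks is the contrast between arms.
- **That four times the participants are needed.** This requires an SD that does not change with the recall window. With overlapping windows and independent daily variation the factor is 1 to 2.
- **That worsening asthma would be missed as a safety matter.** Section 5 draws no safety conclusion from questionnaire scores. It also has any condition present at screening that deteriorates during the study recorded as an adverse event, so worsening has a separate route.

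**Conclusion.** The mismatch is real and can be read directly from the protocol: a two-week intervention is followed by forms that ask about four weeks, so 14 of 28 recalled days precede randomisation. That 50% assumes only that the final form is completed when the intervention ends and that the baseline instruments are reused.

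The consequence is moderate. Under roughly equal weighting of days, the between-arm contrast on quality of life and asthma control is pulled towards zero by up to about half, in favour of neither arm. The loss of power cannot be fixed more closely than a sample-size factor of about 1 to 4. A reader might infer a flaw in the main result of Study V, but the immune, endocrine and metabolomic outcomes do not depend on recall and are untouched. The point is an inexpensive improvement to supporting measures, worth making before recruitment because it cannot be repaired afterwards.

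**What to change.** At both the baseline and the final visit of Study V, use quality-of-life and asthma-control forms with a recall no longer than the two-week intervention, preferably existing validated short-recall versions and not reworded items. State in 4.1.5 which form and which recall period apply at each visit.

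If the four-week forms are kept, state that their scores are reported descriptively and that the absence of a difference will not be read as evidence that step reduction has no effect on quality of life or asthma control.

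The change needs no extra visits, participants or procedures. It costs some comparability with published four-week scores and requires a check that a Portuguese version of each short-recall form is available. Items reworded locally would be untested, and a recall shorter than two weeks would leave out the early part of the intervention. Both should be weighed when the form is chosen.
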